# Effects of *sang-qi* granules on blood pressure and endothelial dysfunction in stage I or II hypertension: study protocol for a randomized double-blind double-simulation controlled trial

**DOI:** 10.1186/s13063-019-3690-z

**Published:** 2020-01-06

**Keywords:** Hypertension, Endothelial dysfunction, Traditional Chinese medicine (TCM), *Sang-qi* granules

## Abstract

**Background:**

Worldwide, hypertension is an important public health challenge because of its high prevalence and the concomitant risks of cardiovascular disease. It induces half of the coronary heart disease and approximately two-thirds of the cerebrovascular disease burden. Vascular endothelial dysfunction has important roles in the pathophysiology of essential hypertension. Types I and II hypertension can be treated with *sang-qi* granules (SQG), a Chinese herbal formula. Several experimental studies on animals have shown that SQG can lower blood pressure and myocardial fibrosis by suppressing inflammatory responses. However, no standard clinical trial has confirmed this. Whether SQG can improve endothelial cell function is unknown.

**Methods/design:**

In this randomized double-blind double-simulation controlled trial, 300 patients with stage I or II hypertension will be recruited and randomly allocated in a 1:1:1 ratio to group A (treatment with SQG and placebo instead of Losartan), group B (treatment with Losartan and placebo instead of SQG), and group C (treatment with SQG and Losartan). In this study, 10 g of SQG (or its placebo) will be administrated twice a day and 50 mg of Losartan (or its placebo) will be administrated once in the morning. The primary endpoint is the drug efficiency for each of the three groups. The secondary endpoints are the change in average systolic and diastolic blood pressure during the day and the night, the change in the rate at which blood pressure drops at night, assessment of target organ damage (heart rate variability, ankle–brachial pressure index, and pulse wave velocity), assessment of any improvement in symptoms (Hypertension Symptom Scale, syndrome integral scale in traditional Chinese medicine, Pittsburgh Sleep Quality Index Scale, Self-Rating Anxiety Scale, Self-Rating Depression Scale, and the 36-Item Short Form Health Survey), blood lipids, serum indicators of vascular function (changes in serum levels of ET-1, TXA2, NO, and PGI2), and safety indicators.

**Discussion:**

This study aims to provide clinical evidence on the efficacy and safety of SQG in the treatment of hypertension. Moreover, the possible mechanism by which SQG may lower blood pressure will be explored by observing the protective effect of SQG on vascular endothelial function, as well as its effect on related clinical symptoms, risk factors, and the target organs of hypertension.

**Trial registration:**

Chinese Clinical Trials Registry, ChiCTR1800016427. Registered on 1 June 2018.

**Electronic supplementary material:**

The online version of this article (10.1186/s13063-019-3690-z) contains supplementary material, which is available to authorized users.

## Background

Hypertension, a major cause of cardiovascular disease, has become a leading global health challenge. Meta-analyses of observational studies show that hypertension is associated with an increased risk of cardiovascular disease, end-stage renal disease, subclinical atherosclerosis, and all-cause mortality [1]. Although there are very beneficial strategies for treating hypertension, such as evidence-based methods for alleviating risk factors and use of angiotensin-converting enzyme inhibitors, β-blockers, etc., outcomes could be better, since hypertension is often not completely controlled. Data for 38,276 adults who participated in the National Health and Nutrition Examination Survey demonstrate that the age-standardized prevalence of hypertension decreased from 48.4% in 1999–2000 to 45.4% in 2015–2016. However, the absolute burden of hypertension consistently increased, from 87.0 million in 1999–2000 to 108.2 million in 2015–2016 [2]. In addition, more than one-fourth of Chinese adults have hypertension and its prevalence in China has increased significantly in recent decades [3].

As a complex condition, the precise cause of essential hypertension is unknown [4]. One potential mechanism is endothelial dysfunction. The endothelium plays a vital role in regulating vascular tone, cell growth, and the interaction between leukocytes, thrombocytes, and the walls of blood vessels [5]. Endothelial cells can produce a variety of substances critical for the maintenance of vascular homeostasis, with nitric oxide (NO) being the most important [6]. When NO is released from endothelial cells, it relaxes the smooth muscle, which results in vasodilation. Many studies have suggested that endothelial dysfunction is an early event in the pathophysiology of essential hypertension. It may contribute to subclinical target organ damage and the progression of atherosclerosis [7]. Thus, endothelial dysfunction has emerged as a promising therapeutic target for treating hypertension.

An early mention of hypertension occurs in the *Huangdi Neijing*, a classic work on traditional Chinese medicine (TCM). Hypertension was classified as headaches and vertigo in ancient China. At that time, traditional Chinese herbal medicine was used to treat the disease, but there was no medical research looking for evidence of efficacy. *Sang-qi* granules (SQG) comprise traditional Chinese herbs used to treat hypertension. Its main ingredients are *Loranthus parasiticus* (*sangjisheng*), *Lycium barbarum* L. t (*gouqizi*), *CassiatoraL tora* Linn. (*juemingzi*), *Dendranthema indicum* (*yejuhua*), and *Salvia miltiorrhiza* Bunge (*danshen*). Our team has conducted a nano liquid chromatography–mass spectrometry analysis of SQG to evaluate its chemical components. It mainly contains betaine, chlorogenic acid, rutin, montfermanin, hesperidin, tanshinone, and quercetin. Previous animal studies by us show that SQG can lower blood pressure and myocardial fibrosis by suppressing inflammatory responses, such as upregulating the expression of PPAR and downregulating the expression of TNF-α, MCP-1, and TGF-β1/Smads, which are signaling molecules involved in myocardial fibrosis pathogenesis in cardiomyocytes [8]. Studies have confirmed that inflammation leads to the development of hypertension and is also a key factor in endothelial dysfunction [9]. Therefore, SQG may be able to regulate vascular endothelial function and may lower blood pressure by inhibiting the inflammatory response (Fig. 1). Consequently, we designed this clinical study to assess the efficacy and safety of SQG on treating endothelial dysfunction in hypertension.

**Fig. 1 Fig1:**
[figure not shown]
Schematic illustrating the relationship among inflammation, endothelial dysfunction, and hypertension. SQG may reduce the blood pressure and improve vascular endothelial function due to its anti-inflammatory properties. SQG *sang-qi* granules

## Methods/design

### Objectives

Our study aims to assess the clinical effect of SQG on vascular endothelial dysfunction in patients with stage I or II hypertension, to provide a reliable experimental basis for the early prevention and treatment of target organ damage in hypertension, and to observe whether TCM plus Western medicine has a better curative effect than Western medicine alone.

### Design

This study is a randomized double-blind double-simulation controlled trial. Participants will be recruited from the China–Japan Friendship Hospital through notices at the hospital and newspaper advertisements.

This clinical trial will recruit patients with stage I or II hypertension, and it will determine the efficacy and safety of SQG. All examinations and tests will be carried out according to the clinical trial plan. Participants will be randomized before the first treatment. Altogether, 300 subjects with stage I or II hypertension will be randomly assigned to three groups in a 1:1:1 ratio: group A (treatment with SQG and placebo instead of Losartan), group B (treatment with Losartan and placebo instead of SQG), and group C (treatment with SQG and Losartan) (Fig. 2). Recruited patients will receive an 8-week treatment (10 g of SQG or the placebo for SQG will be given twice a day in the morning and evening, and 50 mg of Losartan or the placebo for Losartan will be given every morning). SQG and its placebo are produced in China in accordance with the quality standards prescribed in the *Chinese Pharmacopoeia*
http://wp.chp.org.cn/front/chpint/en/. Upon completion of the 8-week treatment, follow-up tests will be conducted at weeks 2, 4, 6, and 8 after randomization.

**Fig. 2 Fig2:**
[figure not shown]
Flowchart of this study

### Recruitment

Patients with hypertension, recruited in the relevant clinic and ward of the China–Japan Friendship Hospital through advertisements and referrals, will be screened. The principal investigator, together with a well-trained attending physician, will identify potentially eligible patients based on the eligibility criteria. Then, a researcher will inform the patient face to face of the whole schedule, including the aim, procedures, possible side effects, and benefits of the study and SQG. If a patient agrees to take part in the study, they must voluntarily sign the informed consent form before randomization. The inclusion, exclusion, and withdrawal criteria are listed in Fig. 3.

**Fig. 3 Fig3:**
[figure not shown]
Inclusion, exclusion, and withdrawal criteria

### Ethics

The protocol (version 1.0, dated 30 March 2018) was approved by the clinical research ethics committee of the China–Japan Friendship Hospital (approval 2018–59-K43), where the study will take place. It has been registered with the Chinese Clinical Trial Registry (ChiCTR1800016427), which is listed in the WHO Registry Network. The trial complies with the principles of the Declaration of Helsinki and the principles of good clinical practice [10, 11]. Each participant must sign an informed consent form before enrollment, and they have right to withdraw from the trial at any time. Additional file 1 is the populated SPIRIT checklist.

### Randomization and blinding

Randomization Biostatisticians used Statistical Analysis System (SAS, Version 9.4) to generate random tables. All the selected patients were included in the clinical trial according to the order of random table numbers. The ratio of three groups was1:1:1.

Blinding the allocation code for each participant was placed in one of 300 sealed opaque envelopes. The envelopes also contained details of the treatment options, possible adverse events, and emergency measures. The envelopes were not accessible to the researchers, participants, clinical trial pharmacists, data managers, or statisticians, none of whom know the location of the envelopes nor the treatment plan for any participants. The drug was similar to its placebo in each group. The manufacturer labeled the random codes on the package according to the principles of GCP.

### Intervention

SQG (production batch number 181201), the placebo for SQG (production batch number 181201), and the placebo for Losartan (production batch number 181001) were produced and packed in a single batch by Jiangxi Puzheng Pharmaceutical Co., Ltd. (Unified Social Credit Identifier 91360823744294486X). As tested, the drug conformed with the quality specified in the Chinese medicine standards published by the State Food and Drug Administration. The batch of SQG was made from 200 kg of original drug flow paste and 180 kg of dextrin. The batch of the placebo for SQG was made from 5 kg of caramel, 120 kg of dextrin, and 25 kg of original drug flow paste. The main component of the placebo for Losartan is dextrin. Losartan was bought from Pharmaceutical Branch of China Pharmaceutical Holdings Beijing Co., Ltd. (Unified Social Credit Identifier 91110101101297579G).

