### Statistical analysis

#### Sample size calculation

The trial will check for superiority between group B (treatment with Losartan and placebo instead of SQG) and group C (treatment with SQG and Losartan), and for non-inferiority between group A (treatment with SQG and placebo instead of Losartan) and group B (treatment with Losartan and placebo instead of SQG).

The sample size was estimated based on clinical research literature and preliminary clinical data on blood pressure and FMD for hypertensive subjects. Given a type-I error rate of α=0.025 and a type-II error rate of β=0.1. The efficiency of the group C was estimated as 90%, and the group B as 70%. Superior efficiency cutoff is 10%. The calculation result was 78 patients in group B and group C by PASS 11 software. After considering the expulsion rate and the requirement of minimum case number of the GCP (A randomized controlled clinical trial requires at least 100 patients each group). We estimated 100 patients in group B and group C. Group A was an exploratory trail with the above two groups, 100 patients initially identified. Above all, we decided to recruit 300 patients during this trail.

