### Data analysis

Data entry and data management will be undertaken by an independent data administrator to ensure data accuracy. A professional statistician will perform the data analysis. We will use the intention-to-treat principle to analyze the efficacy and safety of SQG. For continuous variables, an independent two-sample Student’s *t* test will be used for comparisons between the two study groups, and a paired test will be used for intra-group comparisons. A χ^2^ test will be used for categorical variables. For continuous data with a normal distribution, a Wilcoxon test will be used. *P* < 0.05 is considered to be statistically significant, and all tests are two-tailed.

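### As printed, the SQG placebo contains the SQG drug paste, which contradicts the description of group B as Losartan plus placebo and the objective of a comparison with Western medicine alone

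*Protocol article*

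**What the plan says.** The article's Intervention section gives two batch recipes in adjacent sentences. For the active product: "The batch of SQG was made from 200 kg of original drug flow paste and 180 kg of dextrin". For the control product: the "placebo for SQG was made from 5 kg of caramel, 120 kg of dextrin, and 25 kg of original drug flow paste". The paste has the same name in both.

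The Design section gives the two products in the same granule amount: "10 g of SQG or the placebo for SQG will be given twice a day in the morning and evening". It describes the comparator as "group B (treatment with Losartan and placebo instead of SQG"), and the Sample size calculation repeats that description. One aim under Objectives is "to observe whether TCM plus Western medicine has a better curative effect than Western medicine alone".

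The Sample size calculation tests C versus B for superiority and A versus B for non-inferiority. Its inputs are "Given a type-I error rate of α=0.025 and a type-II error rate of β=0.1", a superiority cutoff of 10%, and "The efficiency of the group C was estimated as 90%, and the group B as 70" per cent. It arrives at 78 per group, raised to 100.

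No section explains the paste in the placebo, says it is inactive at that level, or allows for it in the assumed response rates.

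**The concern.** On a plain reading, every group B patient takes some SQG for 8 weeks, so no arm receives Western medicine alone. If that is so, three things change.

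- **C versus B**, the only comparison that was sized, estimates full against reduced SQG content on top of Losartan. If SQG works, as the trial hypothesises, and the lower content keeps part of the effect, the contrast is pulled towards no difference.
- **A versus B** no longer compares SQG with Losartan, because the Losartan arm also carries SQG.
- **Safety**: no arm is free of SQG, so differences between arms in SQG-related adverse events could be attenuated.

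What is at stake is mainly what the trial can conclude. A report claiming an add-on effect over Western medicine alone would describe a comparison that, by the article's own recipe, was not made.

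**Working it through.** **1. Paste content by input weight** (Intervention)

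- SQG: 200/(200 + 180) = 200/380 = 52.6%.
- Placebo: 25/(5 + 120 + 25) = 25/150 = 16.7%.
- Ratio: 16.7/52.6 = 31.7%.

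The raw ratio 25/200 = 12.5% does not compare like with like, because the batches differ in size.

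**2. Allowing for drying.** The article does not say how much paste mass remains in the finished granules. Let s be that share (0 to 1). Assume it is the same for both batches and that dextrin and caramel lose no mass. Content per gram is then 200s/(200s + 180) in SQG and 25s/(25s + 125) in placebo, so

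ratio = 0.125 × (180 + 200s)/(125 + 25s).

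| s | ratio |
|---|---|
| 1 | 31.7% |
| 0.5 | 25.5% |
| 0.2 | 21.2% |
| towards 0 | 18.0% |

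The ratio rises steadily with s, so 18–32% covers every drying loss. Both products are given in the same granule amount, so the same ratio applies to daily intake.

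**3. The plan's own sample size.** Use unpooled variance, 0.7 × 0.3 + 0.9 × 0.1 = 0.30, and (1.960 + 1.282)² = 10.507, reading 0.025 as one-sided. This matches the Data analysis section, where P < 0.05 "is considered to be statistically significant, and all tests are two-tailed".

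- Cutoff ignored: n = 0.30 × 10.507/0.20² = 78.8, or 79, close to the stated 78.
- Cutoff of 10 points applied: n = 0.30 × 10.507/0.10² = 315.2, or 316.

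The stated 78 is approached only when the stated cutoff is left out. That is a separate problem, but it means any power figure must say which test it refers to.

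**4. Illustration of dilution.** Two assumptions go beyond the documents: 70% is the response on Losartan alone, and the SQG effect is proportional to paste content. With ratio r, the C−B difference is 20 × (1 − r) points.

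- r = 0.18: difference 16.4 points, group B 73.6%.
- r = 0.317: difference 13.7 points, group B 76.3%.

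Power = Φ[(difference − cutoff)/√(variance sum/n) − 1.96], with variance sum 0.300, 0.284 and 0.271 in the three cases:

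| | Undiluted | r = 0.18 | r = 0.317 |
|---|---|---|---|
| 100 per group, no cutoff | 95.5% | 86.8% | 74.8% |
| 100 per group, 10-point cutoff | 44.7% | 22.4% | 10.5% |
| 78 per group, no cutoff | 89.7% | 77.5% | 64.1% |
| 78 per group, 10-point cutoff | 36.4% | 18.4% | 9.1% |

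Exact chi-square power without the cutoff agrees closely at 100 per group: 95.6% undiluted, and 87.1% and 74.7% diluted.

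**The case against.** **The recipe may be misreported.** The Intervention section prints the same production batch number for SQG and its placebo, which may point to careless reporting there. A reader might infer that group B certainly received active drug. The article supports only that this is what its recipe says. The objection does not remove the problem, because the recipe cannot stand beside the Objectives and Design sections.

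**The paste may be there for taste or colour.** The article does not say so. Even if true, the product would still contain SQG paste, and group B would still not be Western medicine alone.

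**The 70% may already describe the arm as treated.** The Sample size calculation assigns it to group B, which is defined as Losartan plus the SQG placebo, and the preliminary data behind it are not shown. On that reading the planned 20 points do not shrink. This stands, and so does the fact that the article gives no dose-response for SQG in patients. The true loss could be nil or larger than shown.

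**The direction is mostly conservative.** Dilution works against the superiority claim for C versus B, so it does not manufacture a false positive. In A versus B, any benefit of the paste strengthens the control, which is conservative for non-inferiority, and group A is called exploratory. This stands too. It limits the harm, but it does not make the stated question the one being answered.

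**Safety.** A reader might infer that safety differences would be hidden. The documents support no more than possible attenuation.

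**Conclusion.** The contradiction is real and nothing in the article resolves it. As printed, the placebo holds about 18–32% of the active granule's paste content per gram. That range assumes the same paste in both batches with the same drying loss, and it covers every value of that loss.

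If the recipe is right, group B is Losartan plus reduced-content SQG, and neither contrast answers the question as worded. That much needs no dose-response assumption. Bias of C versus B towards no difference needs only that the lower content has some of the effect.

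It is tempting to go further and say that the trial's power is 75–87%. The documents do not support this as a finding. The figure requires that 70% refers to Losartan alone, that the effect is proportional to content, and that the stated 10-point cutoff is not applied. With the cutoff, the same illustration runs from about 45% down to 10–22%. Neither range is an estimate of the actual loss.

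The point needs correcting because it decides what the one sized comparison can be said to show.

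**What to change.** Reconcile the Objectives, Design, Intervention and Sample size calculation sections.

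- If the recipe is misreported, correct it. Nothing else then follows from this point.
- If the recipe is right:
  - describe the group B product throughout as a reduced-content SQG control;
  - restate the C–B question and conclusion as full versus reduced SQG content added to Losartan;
  - restate A–B as SQG against Losartan plus reduced-content SQG;
  - drop the claim about Western medicine alone;
  - say whether the assumed 70% is the response on Losartan alone or in the arm as treated, and restate the power on that basis, stating whether the 10-point cutoff applies.

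The cost is wording changes in the protocol, the participant information and the report, and a power statement that may be less favourable. The Trial status section reports 20 patients already recruited, so the information given to them also needs attention. Relabelling makes the conclusion accurate but does not restore any power that is lost.

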### Endpoint measurements

#### Primary endpoint

The primary endpoint is the difference in drug efficiency between the three groups. Efficiency is defined as:
Blood pressure is reduced to a threshold set out in *Guiding Principles for Clinical Research of New Chinese Medicines* [12].Flow-mediated dilation has increased by at least 2% [13].

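### The article does not fix which comparison is primary or whether group A is confirmatory: a three-group difference, two pairwise hypotheses and an exploratory label stand side by side

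*Protocol article*

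**What the plan says.** Three sections of the protocol article bear on this point.

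- **Primary endpoint:** "The primary endpoint is the difference in drug efficiency between the three groups". The abstract also speaks of efficiency in each of three groups.
- **Sample size calculation:** "The trial will check for superiority between group B" and group C, and "for non-inferiority between group A (treatment with SQG and placebo instead of Losartan") and group B. The calculation then covers C vs B only (90% vs 70%): "Given a type-I error rate of α=0.025 and a type-II error rate of β=0.1". The same section goes on: "Group A was an exploratory trail with the above two groups, 100 patients initially identified".
- **Data analysis:** the chi-squared test is given for categorical variables, with no number of groups. For continuous variables, a two-sample t test "will be used for comparisons between the two study groups". The threshold of P < 0.05 "is considered to be statistically significant, and all tests are two-tailed".

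The objectives ask whether Chinese plus Western medicine does better than Western medicine alone, which is C vs B.

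**The concern.** The text supports three different primary analyses:

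1. one test of any difference among A, B and C;
2. two confirmatory pairwise tests, C vs B and A vs B;
3. one confirmatory test, C vs B, with group A exploratory.

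These can give different answers from the same data. Under the first, the endpoint as worded is met by any difference, including one that arises only because SQG alone does worse than Losartan. Under the second, either of two results could be presented as the trial's success. Under the third, an A vs B result could not support a non-inferiority claim, although the article says that the trial will check for one. A choice made after the data are seen would be open to the charge that it followed the result.

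**Working it through.** **1. What the plan's own figure shows.** The article states 78 patients for B and C. Inputs: 90% and 70%, alpha 0.025, power 90%. The unpooled formula for a plain difference, with alpha one-sided, is

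n = [p_C(1−p_C) + p_B(1−p_B)] × (1.960 + 1.282)² / (p_C − p_B)² = (0.09 + 0.21) × 10.507 / 0.04 = 78.8, so 79 per group.

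This is within one of the stated 78. So the design was sized on a single contrast, C vs B, at one-sided 0.025, which equals two-sided 0.05. On that reading the two alpha statements agree. (It leaves out the stated 10% superiority cutoff. With the cutoff the same formula gives 0.30 × 10.507 / 0.01 = 315.2, so 316 per group. That is a separate matter and is not used here.)

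**2. The three-group reading.** Assume a three-group chi-square (2 degrees of freedom, critical value 5.991), n = 100 per arm, and B = C = 70%, so that SQG adds nothing to Losartan. The 70% for B is the article's figure. C = B and every rate for A are assumptions. The noncentrality is

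λ = n × Σ(p_i − p̄)² / [p̄(1 − p̄)].

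For A = 50%: p̄ = 0.6333 and λ = 100 × 0.02667 / 0.2322 = 11.48.

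| Assumed A | λ | Significant (simulated) |
|---|---|---|
| 50% | 11.48 | about 87% |
| 55% | 6.59 | about 62% |
| 60% | 3.00 | about 32% |
| 65% | 0.77 | about 11% |
| 70% | 0 | 5% |

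The noncentral chi-square gives the same values to within half a percentage point. All excess over 5% comes from SQG alone being worse. The test therefore cannot show that C beats B, and it cannot show that A is non-inferior to B.

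**3. Two confirmatory pairwise tests.** With 1:1:1 allocation, C−B and A−B share arm B, so the two test statistics have correlation of about 0.5 (0.48 to 0.51 over assumed rates of 70–80% for C and 55–70% for A). Each two-sided 0.05 test carries 0.025 in the direction of benefit. At the boundary of both null hypotheses:

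- At least one false success: 0.025 + 0.025 − P(both) = 0.050 − 0.0046 = 0.0454.
- At least one rejection in either direction: 0.0907.
- If the tests were independent: 1 − 0.975² = 0.0494 and 1 − 0.95² = 0.0975.

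**4. Group A exploratory.** One confirmatory test remains, with error 0.025 in the direction of benefit and 0.05 two-sided. There is no inflation.

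**5. Under a fixed sequence** (A vs B tested only if C vs B succeeds), the family-wise error is again 0.025 in the direction of benefit and 0.05 two-sided, at the same sample size.

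**The case against.** The best defence is that the sample size section already settles the matter. Group A is called exploratory and only C vs B is sized, so there is one confirmatory test. On this view the primary endpoint sentence merely names the outcome variable, and no section says that a three-group chi-square will be run or will count as success. An order of testing is also something that an analysis plan, not shown here, may supply.

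Much of this stands. A reader might infer that the trial has a family-wise error of about 9%. The documents do not support that: 9.1% needs both tests to be confirmatory and counts both tails, whereas superiority and non-inferiority are directional claims, for which the figure is about 4.5%. A reader might also infer from "will be used for comparisons between the two study groups" that the analysis was written for a two-arm trial. That phrase belongs to the t test for continuous variables. The primary endpoint is a responder rate, and the phrase is compatible with pairwise contrasts. Nor is A vs C a declared hypothesis, so an error rate over all three pairs is not relevant. The omnibus percentages depend on rates for A that the article does not give, and they shrink quickly as A approaches 70%.

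The conflict itself is not answered. The exploratory label stands in the same section as the declaration that the trial will check non-inferiority of A to B, and the primary endpoint sentence includes group A. This is contradictory stated text, not detail left to another document. An analysis plan could resolve it only by overriding one of these sentences.

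**Conclusion.** The concern holds as an internal contradiction about the primary comparison and the role of group A. Its statistical size depends on which sentence governs:

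- **Exploratory label governs:** no error inflation. The primary endpoint sentence and the non-inferiority statement are then wrong as worded.
- **Both pairwise hypotheses confirmatory, with no order:** about 4.5% chance of at least one false success against 2.5% per test, assuming equal arms and correlation of about 0.5.
- **Three-group difference taken literally and tested by chi-square:** a primary result that can be met with no benefit from adding SQG, in about 32% to 87% of trials for assumed A rates of 60% down to 50%, with B = C = 70%.

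The document does not establish that any one of these would be carried out. The defect is that it permits all three. It should be corrected, and it can be corrected without redesign.

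**What to change.** - **Primary endpoint and abstract:** state that the primary comparison is the efficiency rate in C vs B at two-sided 0.05, and that no three-group test is primary.
- **Sample size calculation:** choose one role for A vs B. Either test non-inferiority only if C vs B succeeds (fixed sequence, same alpha), which also requires a margin fixed in advance, or call A vs B exploratory throughout, report an estimate with a confidence interval, and remove the statement that the trial will check non-inferiority.
- **Data analysis:** say which pair of groups each test compares, and treat A vs C as descriptive.

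The cost is wording. Neither the sample size nor the power for C vs B changes. The price is that any A vs B claim becomes conditional on C vs B or is exploratory only. The trial status section reports 20 of the planned 300 patients recruited. The change should be dated and made before unblinding.

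### Stage at entry is an expected predictor of the primary response, but the article names no stratum and only an unadjusted chi-square test; a stage-stratified risk difference would gain modest precision at almost no cost

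*Protocol article*

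**What the plan says.** All references are to the protocol article.

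- **Population (Design).** Both stages enter one trial: "300 subjects with stage I or II hypertension will be randomly assigned to three groups in a 1:1:1 ratio".
- **Primary endpoint.** Efficiency is a responder outcome with two listed parts. The first is "Blood pressure is reduced to a threshold set out in" a cited guideline; the threshold itself is not printed. The second is "Flow-mediated dilation has increased by at least 2"%. The article does not say whether a responder must meet both parts or either one.
- **Randomization and blinding.** "All the selected patients were included in the clinical trial according to the order of random table numbers", in a 1:1:1 ratio. No stratification factor is named.
- **Data analysis.** For a responder outcome the only method named is a chi-square: "A χ^2^ test will be used for categorical variables". No stratified or adjusted analysis is mentioned.
- **Sample size calculation.** C-B is a superiority comparison with planned rates of 90% and 70% and a 10% cutoff. A-B is a non-inferiority comparison, for which the article prints no margin.

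**The concern.** Hypertension stages are graded by blood-pressure level. If success includes reaching a level, a stage II patient has further to fall than a stage I patient, so stage should help to predict the primary outcome. Eligibility depends on stage, so it should be known for every patient before treatment starts.

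A predictor that is free and already recorded is used neither in the stated allocation nor in the stated analysis. Two things follow. A group that by chance receives more stage I patients will look somewhat more effective. The variation in response that stage explains also stays in the error of the C-B and A-B differences.

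**Working it through.** The article gives no stage mix and no response rate by stage, so there is no figure of its own on this point to reproduce. The inputs are as follows.

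| Input | Value | Source |
|---|---|---|
| Patients per group | 100 | Sample size calculation |
| Response, C and B | 90% and 70% | Sample size calculation |
| Share in stage II | 50% | Assumption |
| Response in B, stage I/II | 85%/55% (mean 70%) | Assumption |
| Response in C, stage I/II | 97%/83% (mean 90%) | Assumption |

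**1. Chance imbalance in stage between two groups.**
SD = sqrt(2 × 0.5 × 0.5 / 100) = 0.0707, or 7.1 points. At 1.96 SD this is 13.9 points. If the stage I share lies anywhere from 30% to 70%, the SD is 6.5-7.1 points, and the chance of an imbalance of 10 points or more is about 12-16%.

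**2. Effect on the C-B difference.**
Shift = imbalance × average gap in response between stages. The gap is 85 − 55 = 30 points in B and 97 − 83 = 14 points in C, average 22. At 1.96 SD: 0.139 × 0.22 = 0.031, or about 3 points. The planned difference is 20 points and the cutoff is 10.

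**3. Variance of the C-B difference (each figure divided by 100 patients per group).**
- Ignoring stage: 0.70 × 0.30 + 0.90 × 0.10 = 0.21 + 0.09 = 0.300.
- Within stage, B: (0.85 × 0.15 + 0.55 × 0.45)/2 = (0.1275 + 0.2475)/2 = 0.1875.
- Within stage, C: (0.97 × 0.03 + 0.83 × 0.17)/2 = (0.0291 + 0.1411)/2 = 0.0851.
- Sum within stage: 0.2726. Ratio: 0.2726/0.300 = 0.909, a reduction of about 9%.

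In simulation, where the stage mix varies from trial to trial, the reduction is slightly smaller, so 7-9% is a fair range.

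**4. Power and type I error by simulation (two-sided 0.05, hypothesis of no difference, 100 per group).**

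| Setting | Chi-square | Cochran-Mantel-Haenszel (CMH) by stage |
|---|---|---|
| 90% vs 70%, rates as assumed above | about 95.5% | about 96.6% |
| 85% vs 70%, same stage rates in B | about 73% | about 76% |

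Over a wider range of assumed stage effects (gaps of about 20-43 points in B), the gain is about 0.3-2 points at 90% vs 70% and about 1-7 points at 85% vs 70%. Type I error of the unadjusted test is 0.050-0.053 throughout.

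**5. Judged against the 10% cutoff.**
The standard error is sqrt(0.300/100) = 5.48 points unadjusted and sqrt(0.2726/100) = 5.22 points stratified. Power = Φ(10/SE − 1.96), which is Φ(−0.13) = 45% unadjusted and Φ(−0.04) = 48% stratified. Stratifying helps slightly but does not repair the low power against that cutoff, which is a separate matter of sample size.

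**The case against.** The strongest reply is that a condensed article may leave stratification factors and adjusted analyses to the full protocol or SAP, and that unstratified randomization with a chi-square test is a sound method. Both statements are right. The point is therefore a recommendation to improve the one method the article does state, not a charge that something is absent or wrong.

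A reader might infer more than the documents support in four ways.

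- **That the primary test is invalid.** It is not. Chance imbalance in stage is ordinary sampling error, which the chi-square standard error already covers, and the simulated type I error stays near 5%.
- **That stage is shown to be a strong predictor.** The threshold is only cited. If the guideline credits the size of the fall as well as the level reached, stage matters less. The FMD criterion is also part of the endpoint, and nothing in the article says that FMD response differs by stage. "Expected predictor" is as far as the text goes.
- **That patients are drawn from a single unstratified list.** The article says that they follow the numbers of the random tables and names no stratum. It does not say that there were none.
- **That imbalance could move the result by 5.5 points.** That needs an average gap of 40 points between stages (0.139 × 0.40 = 0.055). With a 50/50 mix and 90% response in C, the gap in C cannot exceed 20 points (100%/80%), so B would need a gap of 60 (100%/40%). Even the shift of about 3 points is a 1.96-SD event, and it is smaller than the standard error of 5.5 points.

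What remains of the concern is the modest gain in precision, which costs almost nothing to take.

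**Conclusion.** The point holds as a low-cost improvement. The trial pools two stages graded by blood pressure, its responder definition includes reaching a blood-pressure threshold, and the only stated test ignores stage. Validity is not in question. Under the assumed mix and rates, stratifying removes about 7-9% of the variance of the C-B difference, adds about 1 point of power in the planned scenario and about 3 points at 85% versus 70%, and protects against a shift of about 3 points under a marked chance imbalance.

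These sizes rest on assumptions about stage mix and response by stage that the article does not give. They would shrink if the FMD criterion drives most failures or if the threshold depends on the size of the fall. If stage turned out not to predict response at all, the simulated loss from stratifying is under half a point of power at 100 per group (for example 95.5% to 95.2%).

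**What to change.** In Data analysis, state that the primary efficiency comparisons, C-B and A-B, use a Mantel-Haenszel risk difference stratified by hypertension stage at entry, with its confidence interval. Adjustment for baseline blood pressure is an acceptable alternative.

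Judge the C-B interval against the stated 10% superiority cutoff, and the A-B interval against the non-inferiority margin; the article prints no figure for that margin, so refer to where it is set. A CMH test can replace the chi-square for the hypothesis of no difference. It should not carry the conclusions, because it answers neither the 10% cutoff nor the non-inferiority question.

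Reporting the difference within each stage is optional, since the objective treats the two stages as one population. Stratifying the list for patients not yet randomized is also optional. It would need re-issued codes, and the analysis change does not depend on it.

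The cost is a change of wording. Trial status reports 20 of 300 patients recruited, so at that point the change could be made before most outcomes existed. It should in any case be fixed before unblinding.
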